### Study assessments

The schedule of the study assessments is listed in Table 6.

**Table 6 Tab6:** Study assessments

	Screening *(within 7 days of randomization)*^*a*^	End of Protocol Treatment^**b**^ *2 days to 3 weeks*	Follow-up Post-Treatment: 3, 6, 9, 12, 16, 24 months^**c**^ *(± 2 weeks)*
Informed consent	X		
Medical history, handedness	X		
ECOG performance status	X		
Adverse event review	X	X	X
Steroid dose assessment	X	X	X
Urine or serum pregnancy test^d^	X		
Diagnostic MRI scan	X *(within 30 days of randomization)*		X
Quality of life questionnaires	X		X
Neurocognitive testing	X		X
Randomization^e^	X		
Resection with pre- or post-operative SRS		X	

^a^All screening procedures must be completed within 7 days of the treatment start date. Results of tests obtained prior to signing the informed consent conducted as part of the subject’s standard care may be used if performed within 7 days before treatment; ^b^The adverse event review and concomitant/steroid dose assessment will be completed once all study treatments have concluded; ^c^Follow up will commence after the last treatment date. Each follow-up visit has a window of ±2 weeks; ^d^Performed as required as per standard institutional policies; ^e^Randomization will occur after all screening procedures are complete and the patient is found to be eligible for trial

*Abbreviations*: *ECOG* Eastern Cooperative Oncology Group, *SRS* stereotactic radiosurgery

### Participant withdrawal and participant discontinuation

Participants may withdraw from the study at any time at their own request, or they may be withdrawn at any time at the discretion of the investigator or sponsor for safety or behaviour reasons, or the inability of the participant to comply with the protocol required schedule of study visits/procedures.

### Sample size

Group sample size of 44 in standard arm and 44 in the experimental arm (total sample size, 88 patients) achieves 80% power to detect a difference between the group proportions of 0.28. The proportion in the standard arm is assumed to be 0.50 and in the experimental arm is assumed to be 0.78. Two-sided t-tests were used to calculate the sample size. The significance level targeted was 0.05 and the actual significance level achieved by the design is 0.044.

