### Statistical analysis

Two types of population will be analyzed:Intent-to-treat population: All patients will be analyzed in the groups to which they were randomized, regardless of whether they received or adhered to the allocated intervention.Per-protocol population: All patients who fulfil eligibility criteria, received, and adhered to treatment assigned, and completed required assessments. For example, patients who had their resection cancelled or not completed will not be analyzed in the per-protocol population analysis.

Interim analysis for futility and efficacy is planned. One interim analysis is planned when 44 events are seen (approximately 50% of total planned events). The interim analysis will be completed and submitted to the Data and Safety Monitoring Board (DSMB) within 60 days of reaching that event. The Pocock beta spending function is used for early stopping for futility and Lan-Demets O’Brien-Flemming alpha spending function is used for early stopping for efficacy.

Descriptive statistics will be used to report baseline characteristics. The mean and standard deviation will be used to describe normally distributed continuous variables; the median and interquartile range will be used to describe non-normally distributed continuous variables. The t-test will be used to compare the continuous variables and the χ2 test will be used to compare categorical variables between arms. Survival will be estimated using the Kaplan-Meier method and compared between arms with two-sided log-rank tests. Hazard ratios will be estimated using the Cox proportional-hazard models adjusted for baseline and stratification variables. Statistical significance will be based on a two-sided α of 0.05. Statistical analyses will be conducted using the current version of SAS at the time of analysis (SAS Institute, Cary, NC).

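### The stated 80% power is a single-look figure; with the planned interim at half information, 88 patients give about 74–78%, mainly because of the futility boundary

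*Protocol article*

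**What the plan says.** The Sample size section of the protocol article gives 44 patients per arm, 88 in all. On the rates it states: "The proportion in the standard arm is assumed to be 0.50 and in the experimental arm is assumed to be 0.78". With these, the design "achieves 80% power to detect a difference between the group proportions of 0.28". On the test and its level: "Two-sided t-tests were used to calculate the sample size", and "The significance level targeted was 0.05 and the actual significance level achieved by the design is 0.044". The section does not mention an interim analysis.

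The Statistical analysis section plans one interim for both futility and efficacy. It is triggered by 44 events, described as about half of the planned total. On the boundaries: "The Pocock beta spending function is used for early stopping for futility", with a Lan-DeMets O'Brien-Fleming alpha-spending function for efficacy. The section does not say whether the futility boundary is binding. It closes with "Statistical significance will be based on a two-sided α of 0.05" and gives no nominal level for the final test.

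**The concern.** The two sections describe different designs. The power statement fits a trial analysed once, at the end. The analysis section describes a trial that may stop halfway, under a futility rule that spends much of the type II error early. A beta-spending function needs a total beta. If that total is 0.20, the sample size is too small for it; if it is larger, the stated power is wrong. Both statements are printed in the article, so an analysis plan that supplies boundary values could not make them agree.

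The stake is how a negative result is read. The article implies a 20% chance of missing the planned effect. Under its own stopping rules that chance is about 22–26%, and much of it would come as an early futility stop. The DSMB and later readers would judge the result against the wrong miss rate.

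**Working it through.** **Inputs.** From Sample size: 44 per arm, 0.50 versus 0.78, two-sided 0.05. From Statistical analysis: one look, Pocock beta spending, Lan-DeMets O'Brien-Fleming alpha spending. Assumed: information fraction t = 0.5, as the stated 50% suggests.

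**1. Reproduce the stated figures (one look, all 88 patients counted).**
- Normal approximation with pooled null variance: (0.28 − 1.960 × 0.1023) / 0.0979 = 0.811, so power is 79.1%.
- Exact binomial enumeration, pooled z-test: power 80.6%; size 0.0444 when both proportions are 0.50.
- Exact enumeration, t-test: power 79.8%; size 0.0430.

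The 80% and the 0.044 are therefore fixed-sample figures. The 0.044 fits the pooled z-test slightly better than the t-test that the article names.

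**2. Boundaries at t = 0.5.**
- Efficacy, per side: 2[1 − Φ(2.241/√0.5)] = 0.0015, so the interim bound is Z = 2.963 (two-sided p = 0.0031). The final bound that uses the remaining alpha is Z = 1.969 (two-sided p = 0.0490).
- Futility: β ln(1 + (e − 1)t) = 0.20 × 0.620 = 0.124. With a drift of 1.960 + 0.842 = 2.802, the interim mean of Z is 2.802 × √0.5 = 1.981. The futility bound is Φ⁻¹(0.124) + 1.981 = 0.83.

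**3. Power with the interim.** Power = P(Z₁ ≥ 2.963) + P(futility bound < Z₁ < 2.963 and Z₂ ≥ final bound), where Z₁ and Z₂ are bivariate normal with correlation √0.5. For a binding boundary the final bound is lowered until the one-sided error, counting futility stops, is 0.025.

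| Convention | From single-look 80.0% | From exact 80.64% |
|---|---|---|
| Efficacy look only | 79.9% | 80.5% |
| Non-binding, boundary set with β = 0.20, stops obeyed | 75.7% | 76.2% |
| Non-binding, β set equal to the actual type II error, stops obeyed | 73.5% | 74.2% |
| Binding, boundary set with β = 0.20 | 77.1% | 77.7% |
| Binding, β set equal to the actual type II error | 76.2% | 76.9% |

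The probability of a futility stop under the planned effect is 12% with β = 0.20, and 16% in the third row of the first column.

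**4. Check without the normal approximation.** Exact enumeration at 22 and then 44 per arm, with the final bound at 1.969, gives 76.3% for a futility bound of 0.83 and 72.7% for a bound of 1.0. The second is the bound in the third row, and its difference from the table comes from the discreteness of small counts.

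**5. Scale of the shortfall.** Keeping 80% under these boundaries needs an inflation of 1.100 (binding; 88 × 1.100 = 96.8, about 97 patients) to 1.167 (non-binding; 88 × 1.167 = 102.7, about 103 patients).

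**6. The trigger.** The assumed rates imply 44 × 0.50 + 44 × 0.22 = 22 + 9.7 ≈ 32 local failures by 12 months, fewer than the 44 events that open the interim. Half of 88 patients is 44, so the trigger may mean patients rather than failures.

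**The case against.** The strongest reply is that the loss is conditional. Every group-sequential figure above assumes a look at half information. If events means local failures, the 44-event trigger exceeds the roughly 32 expected by 12 months. The look might then never come before the 12-month data are complete, and would cost essentially no power. Likewise, if a non-binding futility bound were crossed but not acted on, power would stay near 79.9%. Both points stand and belong in the restatement. They do not support the printed claim, because the plan describes a look at about 50% with a futility rule meant to be used, and no convention that obeys the rule returned 80%.

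A reader might also infer that the final test overspends alpha. The documents do not support that. No sentence sets the final test at a nominal 0.05. The named alpha-spending function itself lowers the final level to about 0.049, and the two-sided 0.05 reads naturally as the overall level. Even a final test at nominal 0.05 would give only 0.051 overall with futility ignored, and about 0.044 or less with futility stops obeyed.

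A reader might further want power figures that allow for death before 12 months. The article gives neither a mortality rate nor how deaths count in the primary endpoint, and a condensed article may leave both to the full protocol. No such figure is claimed here.

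Finally, 0.044 is arithmetically correct, and Pocock beta spending is a legitimate choice. Neither is an error in itself.

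**Conclusion.** The point holds in a limited form. The 80% is correct for a fixed-sample trial and not for the design the article describes. With one look at half information and the named boundaries, 88 patients give about 74–76% power if a non-binding futility boundary is obeyed, or about 76–78% if it is binding. That is a shortfall of roughly 2 to 6 points from the stated 80%, nearly all of it due to the futility boundary.

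The conclusion rests on the look falling at 50% information, on futility stops being followed, and on the stated rates of 0.50 and 0.78. It concerns the power statement only: no inflation of type I error and no bias in the estimate is shown.

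**What to change.** In Sample size, label 80% and 0.044 as single-look figures, the latter at a common proportion of 0.50. Add that power with the planned interim is about 74–78%, and narrow the range once the futility boundary is declared binding or non-binding. State the assumed information fraction.

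In Statistical analysis, define what counts as an event for the interim, and reconcile the trigger of 44 with the roughly 32 local failures implied by the assumed rates. State that two-sided 0.05 is the overall level and that the final nominal level is about 0.049, to be recomputed at the observed information.

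The change is text only and needs no extra patients. Its cost is a less favourable power statement. A less aggressive futility spending function would recover some power but is optional.

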### Statistical analysis

Two types of population will be analyzed:Intent-to-treat population: All patients will be analyzed in the groups to which they were randomized, regardless of whether they received or adhered to the allocated intervention.Per-protocol population: All patients who fulfil eligibility criteria, received, and adhered to treatment assigned, and completed required assessments. For example, patients who had their resection cancelled or not completed will not be analyzed in the per-protocol population analysis.

Interim analysis for futility and efficacy is planned. One interim analysis is planned when 44 events are seen (approximately 50% of total planned events). The interim analysis will be completed and submitted to the Data and Safety Monitoring Board (DSMB) within 60 days of reaching that event. The Pocock beta spending function is used for early stopping for futility and Lan-Demets O’Brien-Flemming alpha spending function is used for early stopping for efficacy.

Descriptive statistics will be used to report baseline characteristics. The mean and standard deviation will be used to describe normally distributed continuous variables; the median and interquartile range will be used to describe non-normally distributed continuous variables. The t-test will be used to compare the continuous variables and the χ2 test will be used to compare categorical variables between arms. Survival will be estimated using the Kaplan-Meier method and compared between arms with two-sided log-rank tests. Hazard ratios will be estimated using the Cox proportional-hazard models adjusted for baseline and stratification variables. Statistical significance will be based on a two-sided α of 0.05. Statistical analyses will be conducted using the current version of SAS at the time of analysis (SAS Institute, Cary, NC).

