**Methods:**

This multicenter, randomized controlled trial aims to recruit 88 patients with resectable brain metastases over an estimated three-year period. Patients with ten or fewer brain metastases with at least one resectable, fulfilling inclusion criteria will be randomized to postoperative SRS (standard arm) or preoperative SRS (investigational arm) in a 1:1 ratio. Randomization will be stratified by age (< 60 versus ≥60 years), histology (melanoma/renal cell carcinoma/sarcoma versus other), and number of metastases (one versus 2–10). In the standard arm, postoperative SRS will be delivered within 3 weeks of surgery, and all unresected metastases will receive primary SRS. In the investigational arm, enrolled patients will receive SRS of all brain metastases followed by surgery of resectable metastases within one week of SRS. In either arm, single fraction or hypofractionated SRS in three or five fractions is permitted. The primary endpoint is to assess local control at 12 months in both arms. Secondary endpoints include local control at other time points, regional/distant brain recurrence rates, leptomeningeal recurrence rates, overall survival, neurocognitive outcomes, and adverse radiation events including radiation necrosis rates in both arms.

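### The interim trigger of 44 events, described as about half of the planned events, cannot be reconciled with the plan's own rates, which give about 32 local failures by 12 months

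*Protocol article*

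**What the plan says.** The abstract's Methods paragraph names the primary endpoint: "The primary endpoint is to assess local control at 12 months in both arms". The Sample size section sizes the trial on two proportions: "The proportion in the standard arm is assumed to be 0.50 and in the experimental arm is assumed to be 0.78", with 44 patients per arm ("total sample size, 88 patients"). It says this number "achieves 80% power to detect a difference between the group proportions of 0.28".

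The Statistical analysis section then plans a single look for futility and efficacy: "One interim analysis is planned when 44 events are seen (approximately 50% of total planned events". Futility uses a Pocock beta spending function and efficacy a Lan-DeMets O'Brien-Fleming alpha spending function. The results go to the DSMB within 60 days of the trigger. The article gives no definition of an event, no planned final event count and no survival assumption.

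**The concern.** If 44 is about 50% of planned events, about 88 events are planned. There are 88 patients, so this would require an event in every patient of both arms, while the sample size assumes that 50% and 78% of patients have local control at 12 months.

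Both spending functions take the information fraction as their input. If the stated fraction of one half is wrong, the boundaries set at that fraction are wrong as well. If the trigger is too high for the event it counts, the look comes after enrolment has finished, or not at all. Stopping could then no longer spare any patient randomisation. A trigger corrected after unblinded data have been seen would also raise doubts about the type I error, so it should be corrected beforehand.

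**Working it through.** **Inputs from the article.** 44 patients per arm, 88 in total; proportions 0.50 (standard) and 0.78 (experimental), read as local control at 12 months; two-sided α of 0.05; target power 80%; stated actual significance level 0.044; recruitment over about three years; follow-up visits to 24 months; interim at 44 events, called about 50%.

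**1. The plan's sample size reproduces.** For 0.50 versus 0.78 at 44 per arm, the pooled normal approximation gives 79.1% power. Exact binomial enumeration of the pooled two-sided z test gives 80.6% power and an actual α of 0.0444 when both proportions are 0.50, which matches the stated 0.044. The t-test that the section names gives 79.8% and 0.043. The 88 is therefore a number of patients for a comparison of two proportions, not a number of events.

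**2. Planned events implied by the trigger.** 44 / 0.50 = 88, one per patient.

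**3. Expected local failures by 12 months under the plan's rates.**
- Standard arm: 44 × (1 − 0.50) = 22.0
- Experimental arm: 44 × (1 − 0.78) = 9.7
- Total: 31.7, and half of it is 15.8
- Trigger relative to the total: 44 / 31.68 = 1.39
- P(at least 44 failures), from the convolution of Bin(44, 0.50) and Bin(44, 0.22): 0.0034

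**4. Other readings of the same figures.**

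| Reading | Expected total | 44 as a share |
|---|---|---|
| Both arms at 0.50 control | 88 × 0.50 = 44 | 100%; P(at least 44) = 54% |
| 0.50 and 0.78 taken as failure proportions | 22 + 34.3 = 56.3 | 78% |
| Failures to 24 months, nobody dies | 44 × (1 − 0.50²) + 44 × (1 − 0.78²) = 50.2 | 88% |
| Failures to 24 months, 30% dead by 12 months | about 38 | above 100% |
| Failures to 24 months, 50% dead by 12 months | about 30 | above 100% |

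The 24-month rows assume constant hazards. The mortality figures are assumptions, because the article gives none. With uniform accrual over 36 months and no deaths, the 44th failure is expected at about month 43, some seven months after accrual ends.

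**5. An event-driven design does not lead to 88 either.** Under exponential failure the hazard ratio is ln 0.78 / ln 0.50 = 0.358. The log-rank approximation for a fixed design with 80% power gives 4 × (1.96 + 0.84)² / (ln 0.358)² ≈ 30 failures.

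**The case against.** The strongest objection is that "event" is undefined, so reading it as local failure is an inference. Under local failure or death, with constant hazards, 36-month accrual and 24-month follow-up, an assumed 30% dead by 12 months gives about 69 events. Then 44 is 63% of the total and is reached near month 32. With 50% dead the total is about 79, the share is 56%, and 44 is reached near month 28. Both dates fall before accrual ends. This stands as a limit on what can be claimed, but it does not rescue the text: the article does not state this composite, gives no survival rate and does not size the trial on it. Even then, 44 would be exactly half only if all 88 patients had an event.

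A reader might infer that the trial yields only about 32 failures in all and that the interim could never occur before the end. The document does not support that. The figure of 32 counts failures to 12 months, whereas follow-up runs to 24 months. If nobody dies, 44 failures are expected around month 43, after accrual but before the last 24-month visit at about month 60. The scenarios in which 44 is not expected at all rest on assumed mortality.

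A reader might also infer that the DSMB has no usable stopping rule. The article is condensed, and a full protocol, SAP or charter may define the trigger properly. The six-monthly DSMB reviews also continue, although as described they cover matters such as recruitment and adverse events. None of this removes the fault, because the article does state a trigger and a percentage, and the two conflict with its own sample size.

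Finally, the number is probably a slip: 44 is exactly half of the patients. That explains the sentence and makes it easy to repair, but it does not make it correct.

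**Conclusion.** The point holds for the trigger and the information fraction as written, and it must be corrected before the interim. The mismatch for the primary endpoint at 12 months rests only on the plan's own figures, with event read as local failure and no allowance for deaths. Allowing for deaths lowers the failure count further, to about 27 or 24 by 12 months with an assumed 30% or 50% dead by then. What happens beyond 12 months depends on the assumed hazards, accrual pattern and mortality. On the local-failure readings checked, 44 events ranges from 78% of the expected total to more than all of it. It is never half.

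**What to change.** Define the event, and restate the trigger in the unit of the primary test.

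- **If the two-proportion test on which the trial is sized is primary:** hold the interim when 44 randomised patients (half of 88) have reached the 12-month assessment point, and state how deaths before 12 months are handled. Without that rule 44 is not automatically half. If only patients with a known 12-month outcome counted, about 67 or 52 would be available at the end with 30% or 50% dead by 12 months (assumed), and 44 would be 66% or 85% of them.
- **If time to local failure is primary:** state the planned final number of failures (about 32 by 12 months under the plan's rates, fewer with deaths) and hold the interim at half of it, about 16. Sixteen is half only of 32. Against 27 or 24 expected failures it is about 59% or 68%. Under the assumptions above, the 16th failure falls at about months 21 to 27 with 52 to 65 patients enrolled, so stopping could still matter.

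In either case, compute both boundaries at the observed information fraction, and restate the power with the futility boundary included. The stated 80% matches a fixed design (79% to 81% on recalculation), and the article shows no allowance for beta spending.

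The cost is one reworded sentence, carried into any SAP and DSMB charter, recalculated boundaries, and possibly a slightly lower stated power. Whether extra patients would be needed to hold 80% has not been shown either way.

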The ASCO-SNO-ASTRO consensus statement for the treatment of brain metastases with radiosurgery indicates that there is no recommendation regarding the sequencing of surgery and SRS [22]. There are no randomized data comparing preoperative and postoperative SRS currently in the literature [23]. The present study is a prospective, multicenter, randomized, controlled trial comparing preoperative to postoperative SRS in the treatment of resectable brain metastases. Importantly, fractionated SRS for both preoperative and postoperative cases, depending on their size, is allowed in this study. The primary objective of the study is to compare the local control of pre- versus postoperative SRS. Secondary objectives are to compare distant brain recurrence, leptomeningeal recurrence, and overall survival of the two arms as well as the comparison of quality-of-life and neurocognitive outcomes of preoperative versus postoperative SRS (Table 1).

**Table 1 Tab1:** Study endpoints

**1.0 Primary endpoints** 1.1 Local control at 12 months.	
**2.0 Secondary endpoints** 2.1 Local control at 6 and 24 months 2.2 Distance brain recurrence rate (%) at 6,12, and 24 months 2.3 Leptomeningeal recurrence rate (%) at 6, 12, 24 months 2.4 Overall survival (in months) at 6, 12 and 24 months 2.5 Hopkins Verbal Learning Test Revised score (points) at 3, 6, 9, 12, 16, 24 months 2.6 Controlled Oral Word Association test score (points) at 3, 6, 9, 12, 16, 24 months 2.7 Trail Making Test score (points) at 3, 6, 9, 12, 16, 24 months	

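### The 12-month local-control endpoint is sized as two unadjusted proportions with no allowance for death before 12 months, and the adjusted model is not tied to it

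*Protocol article*

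**What the plan says.** Table 1 of the protocol article lists one primary endpoint, "Local control at 12 months", and the Background gives the matching aim: "The primary objective of the study is to compare the local control of pre- versus postoperative SRS".

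The Sample size section plans 44 patients per arm (88 in total) for 80% power to detect 0.50 against 0.78. It adds that "Two-sided t-tests were used to calculate the sample size" and gives an achieved significance level of 0.044. It makes no allowance for death or loss before 12 months.

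The Randomization section stratifies on age, histology and number of metastases. The Statistical analysis section lists a t-test for continuous variables and a chi-square test for categorical ones. Then come "Survival will be estimated using the Kaplan-Meier method and compared between arms with two-sided log-rank tests" and "Hazard ratios will be estimated using the Cox proportional-hazard models adjusted for baseline and stratification variables". None of these is named as the primary analysis of local control. The role of a death before 12 months without local failure is not stated. Overall survival is a secondary endpoint in Table 1, so deaths are expected.

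**The concern.** A patient who dies at 7 months without local failure can be counted as controlled, counted as failed, or left out. Each choice gives a different 12-month proportion, a different treatment difference and a different power. With 44 per arm and the sizing only just at 80%, nothing is in reserve.

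The second part is the randomisation factors. The tests are listed without them, and the model that does use them is not attached to the primary endpoint. The primary p-value could therefore come from an unadjusted test and the effect estimate from an adjusted model.

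**Working it through.** **Step 1. Reproduce the stated design.** Inputs from the Sample size section: 44 per arm, 0.50 and 0.78, two-sided 0.05. Enumerating all outcomes of two binomials with n = 44 and applying the pooled two-proportion (chi-square) test gives power 80.6% and actual size 0.0444 when both proportions are 0.50. This matches the stated 80% and 0.044. A t-test gives 79.9% and 0.0430. So the plan's figure is that of an unadjusted comparison with all 88 patients classified. Expected local failures by 12 months are 44 × 0.50 + 44 × 0.22 = 31.7.

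**Step 2. Add deaths.** The article gives no death rate. Assume that a share q would die by 12 months, the same in both arms and independent of local failure, with constant hazards. With 12 months as the time unit:

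- local-failure hazard h = −ln(S): 0.693 for S = 0.50 and 0.248 for S = 0.78
- death hazard d = −ln(1 − q)
- alive without local failure at 12 months: A = S(1 − q)
- local failure before death by 12 months: F = h/(h + d) × (1 − A)

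For q = 20%, d = 0.223. Standard arm: A = 0.50 × 0.80 = 0.400 and F = 0.693/0.916 × 0.600 = 0.454. Investigational arm: A = 0.624 and F = 0.198. For q = 50%: A = 0.250 and 0.390; F = 0.375 and 0.161.

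The proportion controlled then depends on the coding:

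| Death without local failure | Proportion | q = 20% | q = 50% |
|---|---|---|---|
| No failure | 1 − F | 0.546 vs 0.802 | 0.625 vs 0.839 |
| Excluded | A/(A + F) | 0.468 vs 0.759 | 0.400 vs 0.708 |
| Failure | A | 0.400 vs 0.624 | 0.250 vs 0.390 |

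Under exclusion, the expected numbers analysed fall to 37.6 and 36.2 (q = 20%), or 27.5 and 24.2 (q = 50%).

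Power of the same chi-square test by exact enumeration, averaged over the number analysed where patients are excluded:

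| q | No failure | Excluded | Failure |
|---|---|---|---|
| 10% | 78.0% | 77.2% | 67.4% |
| 20% | 75.0% | 74.2% | 54.2% |
| 30% | 71.6% | 70.7% | 44.7% |
| 40% | 68.0% | 66.5% | 38.0% |
| 50% | 64.2% | 61.6% | 30.2% |

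Simulation of the same scenarios gives 76% to 64%, 75% to 61% and 55% to 31% for q = 20% to 50%, within about one point. Excluding every patient who dies, even after a recorded local failure, gives 70% to 50%.

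**Step 3. What a competing-event analysis changes.** The log-rank test on the cause-specific hazard of local failure (20,000 simulated trials per scenario) gives:

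| q | Follow-up to 12 months | Follow-up to 24 months |
|---|---|---|
| 20% | 75.8% | 90.5% |
| 30% | 73.4% | 87.4% |
| 40% | 70.5% | 83.5% |
| 50% | 66.8% | 78.2% |

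At 12 months the gain over chi-square with deaths as no failure is 1 to 3 points. The higher power in the last column comes from counting later failures under proportional hazards.

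**Step 4. What adjustment changes.** With 40% deaths, follow-up to 12 months and the three factors as main effects in a cause-specific Cox model, power moves from 67.7% to 66.8% if no factor is prognostic. It moves from 69.3% to 69.7% with assumed hazard ratios of 1.2, 1.5 and 1.2, and from 68.6% to 72.5% with 1.5, 2.5 and 1.5. In a separate simulation with 30% deaths, stratifying by histology alone moved power from 77.4% to 82.2% when the factors were strongly prognostic (86.6% to 85.8% when they were not). Crossing all eight strata in the latter case gave 80.8%. The range is about −1 to +5 points, and main effects are safer than eight strata.

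**The case against.** **The document is an article.** The full protocol or analysis plan may name the primary test and the handling of deaths. This stands in part: a reader might infer that the analysis is fixed as a raw proportion, but that is firm only for the sizing. The absence of any allowance for death in the sample size is, however, visible in the article itself.

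**The assumed 0.50 and 0.78 may already be net of deaths.** If they were meant as crude proportions under a chosen coding, the 80% would stand as calculated. The article does not say so, and the coding would still have to be stated.

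**Adjustment is planned.** A reader might infer that the randomisation factors are ignored. The Cox sentence contradicts that. What remains is that the adjusted model is not tied to local control and the listed tests are given without the factors.

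**Kaplan-Meier is named for survival only.** The article does not say that local control will be estimated with deaths censored, so the charge that local failure will be overstated has no basis in the text.

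**A proportion with deaths as no failure is well defined.** True: with complete follow-up it equals the 12-month cumulative incidence. The gap is that the coding is unstated.

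**The time origin.** Table 6 says "Follow up will commence after the last treatment date". Taking two weeks to start treatment, the permitted interval and a five-day course, the latest compliant last-treatment day is 14 + 21 + 5 = 40 (standard) against 14 + 5 + 7 = 26 (investigational). That 14-day difference is no larger than the ±2-week visit window, and the footnote schedules visits rather than defining the endpoint. This is minor.

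**Conclusion.** The point holds in a limited form. The stated 80% power is correct arithmetic for 88 patients who all have a known 12-month status. Under 20% to 50% deaths it is about 75% to 64%, 74% to 62%, or 54% to 30%, depending on how deaths are coded. The coding alone moves power by 21 points (75.0 − 54.2) to 34 points (64.2 − 30.2). These figures rest on an assumed death rate, equal in both arms and independent of local failure, and on constant hazards; the article supplies none of these.

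A reader might infer that an adjusted competing-risk analysis recovers the lost power at no cost. It does not. At 12 months it gains 1 to 3 points over the simple proportion with deaths as no failure, and adjustment adds about −1 to +5. The case for it is a defined estimand and one agreed primary analysis, not recovered power.

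**What to change.** 1. Define the primary endpoint as local failure timed from randomisation, with death without local failure as a competing event.
2. Report 12-month cumulative incidence of local failure by arm (Aalen-Johansen), with the difference and 95% CI. Show death without local failure by arm beside it.
3. Name one primary test adjusted for age, histology and number of metastases as main effects. The Cox model already planned would serve, used as a cause-specific model for local failure.
4. Treat distant and leptomeningeal recurrence in the same way.
5. Restate the power, and the event count for the interim analysis, under a stated death rate and this endpoint definition.

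Cost: changes of wording, slightly more analysis work, and a less favourable stated power. Three covariates would be fitted on roughly 24 to 32 failures by 12 months. The cause-specific test and the cumulative-incidence difference are different quantities and can disagree at the margin, so the plan should say which one decides.

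Using follow-up to 24 months in the test is optional. It raises power, but it changes the estimand and relies on proportional hazards.
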